#### **8.6 Follow-up of subjects withdrawn from treatment**

There is no specific follow-up of the patients, except that the first follow-up scan is used to evaluate the primary endpoint. Therefore, study related follow-up of withdrawn patients is not performed.

#### **8.7 Premature termination of the study**

Reasons for premature termination of the study are:

- Occurrence of serious adverse events that are directly related to the navigation system.

## 9. SAFETY REPORTING

### 9.1 Temporary halt for reasons of subject safety

In accordance to section 10, subsection 4, of the WMO, the sponsor will suspend the study if there is sufficient ground that continuation of the study will jeopardise subject health or safety. The sponsor will notify the accredited METC without undue delay of a temporary halt including the reason for such an action. The study will be suspended pending a further positive decision by the accredited METC. The investigator will take care that all subjects are kept informed.

### 9.2 AEs, SAEs and SUSARs

#### 9.2.1 Adverse events (AEs)

Adverse events are defined as any undesirable experience occurring to a subject during the study, whether or not considered related to the investigational product, trial procedure, or the experimental intervention. All adverse events reported spontaneously by the subject or observed by the investigator or his staff will be recorded.

#### 9.2.2 Serious adverse events (SAEs)

All Serious Adverse Events (SAE) occurring from registration until 30 days after the last protocol treatment/administration should be reported through the web portal *ToetsingOnline* to the accredited METC that approved the protocol. Serious adverse events occurring more than 30 days after the last study medication/treatment will NOT be reported unless the investigator feels that the event may have been caused by the study treatment or a protocol procedure. Study-specific clinical outcomes of death because of disease progression are exempt from serious adverse event reporting, unless the investigator deems them related to use of the device.

A serious adverse event is any untoward medical occurrence or effect that

- results in death;
- is life threatening (at the time of the event);
- requires hospitalisation or prolongation of existing inpatients' hospitalisation;
- results in persistent or significant disability or incapacity;
- is a congenital anomaly or birth defect; or

- any other important medical event that did not result in any of the outcomes listed above due to medical or surgical intervention but could have been based upon appropriate judgement by the investigator.

An elective hospital admission will not be considered as a serious adverse event.

The investigator will report all SAEs to the sponsor without undue delay after obtaining knowledge of the events. The sponsor will report the SAEs through the web portal *ToetsingOnline* to the accredited METC that approved the protocol, within 7 days of first knowledge for SAEs that result in death or are life threatening followed by a period of maximum of 8 days to complete the initial preliminary report. All other SAEs will be reported within a period of maximum 15 days after the sponsor has first knowledge of the serious adverse events.

#### **9.2.3 Suspected unexpected serious adverse reactions (SUSARs)**

Not applicable since we don't investigate a medicinal product

### **9.3 Annual safety report**

Not applicable since we don't have an investigational medicinal product. The investigational medical device has been evaluated on 37 patients in a previous study, without any safety issues.

### **9.4 Follow-up of adverse events**

All AEs will be followed until they have abated, or until a stable situation has been reached. Depending on the event, follow up may require additional tests or medical procedures as indicated, and/or referral to the general physician or a medical specialist.

SAEs need to be reported till end of study within the Netherlands, as defined in the protocol

### **9.5 Data Safety Monitoring Board (DSMB) / Safety Committee**

No data safety monitoring board or safety committee will be appointed.

## 10. STATISTICAL ANALYSIS

### 10.1 Primary study parameter(s)

The main study parameter is the percentage of failed procedures, where failure is defined as: presence of any residual target lymph node on follow-up imaging.

The final percentage of failed procedures in both arms will be compared using a one-sided two-proportion z-test. The evaluation will be done on intention to treat, including the lymph nodes which are marked as inoperable during surgery due to expected morbidity.

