### 4.4 Sample size calculation

In the current pilot study (N13NAV), a total of 71 targeted lymph nodes were identified in 25 patients. In total, we failed to localize 4 of the 71 lymph nodes, in four separate patients. We therefore expect to have approximately 16% (4/25) failed procedures in the navigation arm ( $p_B=0.16$ ). In the current pilot study, surgeons indicated in at least 6 patients that certain localized lymph nodes would have not been found without navigation. We therefore estimate a failure rate of 40% ( $p_A=0.40$ ) in the control arm ((6+4)/25). In our study setup we test the following hypotheses  $H_0: p_A = p_B$  and the alternative hypothesis  $H_1: p_A > p_B$  (one-sided alpha). The number of

needed patients per arm with an alpha of 0.05 and a power of 80% is 41. Accrual of all patients is estimated to take 36 months (excluding the time to the first follow-up scan for all).

[figure not shown]

Fig. 2: Screenshot of the 3D anatomical model of a patient during navigation surgery in which the arteries (red), veins (blue), ureters (yellow), bones (white), and pathologic lymph nodes (lime) are shown. The tracked pointer is manipulated by the surgeon in the pelvis of the patient, and is shown in real-time within the 3D model (green). In this example a lymph node was localized in between the internal iliac artery, the internal iliac vein and the ureter

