## 8.2 Randomisation, blinding and treatment allocation

Patients will be randomized according to a randomization scheme provided by the Trial bureau through a website. The randomization scheme is blinded from the surgeons and investigators. In the randomization we will stratify for surgical sub-specialization (surgery, urology, gynaecology), since differences in their approach to the targeted lymph nodes might exist. After receiving informed consent, the researcher will visit the randomization website, provide the specialism, and the patient will automatically be assigned a study number and treatment arm.

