### 10.3 Other study parameters

- body weight, length, age, gender, type of primary tumour, location of primary tumour, lymph node size, neoadjuvant treatment, previous pelvic surgery, previous pelvic radiotherapy will only be used to evaluate if there is a dis-balance between the arms.
- Correlation between pre-operative imaging findings and pathology: these data will only be used to generate new hypotheses

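### Randomisation is stratified by surgical sub-specialisation but the primary z-test ignores the strata; if failure rates differ between specialties, the test is conservative and loses a little power

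*Protocol*

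**What the plan says.** Section 8.2 sets the allocation and gives a reason: "In the randomization we will stratify for surgical sub-specialization (surgery, urology, gynaecology), since differences in their approach to the targeted lymph nodes might exist".

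Section 10.1 fixes the primary comparison: "The final percentage of failed procedures in both arms will be compared using a one-sided two-proportion z-test". It names no stratum term.

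Section 10.3 does not bring the strata back. The patient and tumour characteristics that it lists "will only be used to evaluate if there is a dis-balance between the arms", and sub-specialisation is not in that list.

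Section 4.4 sizes the trial on the same unstratified comparison. It expects "approximately 16% (4/25) failed procedures in the navigation arm" against 40% in the control arm, and states that the number of "needed patients per arm with an alpha of 0.05 and a power of 80% is 41", with a one-sided alpha.

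**The concern.** Stratified allocation balances the arms within each specialty. Variation in failure rate between specialties therefore largely drops out of the true sampling error of the difference between arms. The pooled z-test takes its variance from the overall failure proportion, so it still counts that variation. Where specialties differ, the standard error and the p-value come out too large.

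The reason given for stratifying is thus close to the condition under which the chosen test does not match the design. What is at stake is efficiency: part of the 5% level may go unused in a trial of 82 patients with little spare power. False positives are not at stake, because the error runs the other way.

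**Working it through.** **1. The plan's own figure.** Inputs from section 4.4: 0.40 and 0.16, one-sided alpha 0.05, power 80%. With unpooled variance,

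n = (1.645 + 0.842)² × (0.40×0.60 + 0.16×0.84) / 0.24² = 40.19, rounded up to 41.

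The stated 41 per arm reproduces. The pooled-variance formula gives 43, and normal-approximation power at 41 per arm is 78.9%.

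**2. Assumed strata.** The protocol gives no failure rates by specialty and no expected case mix. The pilot mix in section 1 (21 colorectal, 12 urologic, 1 gynaecologic, 3 sarcoma) is used, with sarcoma counted as surgery: 24/12/1 of 37. Scaled to 41 per arm, 41×24/37 = 26.6, 41×12/37 = 13.3 and 41×1/37 = 1.1, taken as 27/13/1. These are all 37 pilot patients. The specialty split of the 25 with target lymph nodes is not given.

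**3. Mechanism.** With control failure of 50% in surgery and 20% in the other 14 patients per arm:

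- overall rate (27×0.50 + 14×0.20)/41 = 0.3976, so total variance 0.3976×0.6024 = 0.2395
- within-stratum variance (27×0.25 + 14×0.16)/41 = 0.2193
- ratio 0.2193/0.2395 = 0.916, square root 0.957
- approximate true size 1 − Φ(1.645/0.957) = 1 − Φ(1.719) = 4.3%

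With 54% and 11%: overall rate 0.3932, variances 0.1970 and 0.2386, ratio 0.826, square root 0.909, size 1 − Φ(1.810) = 3.5%. The counts are discrete, which takes the actual size somewhat lower.

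**4. Simulation.** Setting: 27/13/1 per arm, pooled z-test against Cochran-Mantel-Haenszel (CMH) without continuity correction, critical value 1.645. Navigation rates use a common odds ratio chosen so that the overall difference stays at 24 points.

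| Control failure, surgery / other | Power, z vs CMH | One-sided size with both arms at about 40%, z vs CMH |
|---|---|---|
| no difference | about 80% vs 80% | – |
| 45% / 30% | 80.1% vs 80.3% | – |
| 50% / 20% | 80.9% vs 82.0% | 3.9% vs 5.0% |
| 54% / 11% | 82.1% vs 84.0% | 3.2% vs 5.1% |

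If both arms instead fail at the lower navigation-arm rates, the z-test's size in the last two rows is between 4.4% and 4.8%.

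**5. Sensitivity to rounding.** With exactly 41 per arm, 17 against 10 failures gives z = (7/41)/√[(27/82)(55/82)(2/41)] = 1.64491. That lies between the unrounded critical value 1.64485 and 1.645. A recheck with the unrounded value (exact enumeration for z, one million simulated trials for CMH) gives power of 80.5% vs 79.8%, 80.8% vs 80.4%, 81.5% vs 81.8% and 82.6% vs 83.9% down the table. Size in the last two rows is 4.1% vs 5.0% and 3.4% vs 5.1%. The direction holds, and the power gain is smaller.

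**6. Random stratum sizes.** Setting: permuted blocks of 4 (assumed), 82 patients, 200,000 trials, control rates for surgery/urology/gynaecology.

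| Setting | Power, z vs CMH | Size at 40%, z vs CMH |
|---|---|---|
| no difference | 79.9% vs 79.3% | 5.0% vs 5.1% |
| 46/28/37% | 80.2% vs 80.2% | 4.6% vs 4.9% |
| 51/19/33% | 80.6% vs 81.7% | 4.1% vs 4.9% |
| 56/9/27% | 81.4% vs 84.1% | 3.3% vs 5.0% |
| 76/35/9%, equal thirds | 83.0% vs 88.6% | 2.3% vs 4.9% |

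The last row needs both extreme differences and a case mix far from the pilot's.

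**The case against.** An unadjusted test after stratified allocation is a legitimate choice. It controls type I error, it matches the hypotheses and sample size in section 4.4, and it reaches about 80% power in every setting above where the planned 24-point difference holds. All of that stands, so this is not an error of validity.

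The protocol also does not predict that outcomes differ. It says only "since differences in their approach to the targeted lymph nodes might exist", which concerns approach and is a possibility. A reader might infer that the z-test is certain to be conservative. The documents do not support that, since with equal failure rates there is no loss.

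A reader might also infer that ignoring the strata leaves the trial underpowered. Holding the within-stratum odds ratio at (0.16/0.84)/(0.40/0.60) = 0.286 does give z-test power of 76.3% at 50%/20% and 72.9% at 54%/11%. But a fixed odds ratio shrinks the overall effect to 39.8% against 16.9% and 39.3% against 17.7%. With those overall rates and no stratum difference, z-test power is already 75.9% and 71.2%. The drop comes from the smaller effect. Only the gap to the stratified test (77.7% and 75.7%) belongs to the choice of test.

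The objection does not dispose of the mismatch itself. Section 10.1 names a specific unstratified test as primary. An analysis plan that is not shown could add a stratified sensitivity analysis, but could not replace the primary test without departing from the protocol.

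**Conclusion.** The mismatch between allocation and primary analysis is real, and its consequence is small and conditional. If specialties differ in failure rate, the z-test is conservative. With the pilot mix and the planned 24-point difference it loses about 0 to 2 power points across the 27/13/1 settings, and about 3 in the strongest pilot-mix setting with random stratum sizes. One-sided size falls to between 3% and 4% under marked differences with both arms near 40%, and is closer to 5% at lower failure rates.

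These figures rest on assumed stratum rates, on a case mix taken from all pilot patients rather than the lymph-node subgroup, and on an assumed block size. The stated sample size stands and type I error is not inflated. This is a minor improvement in efficiency and consistency.

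**What to change.** In section 10.1:

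- Make the primary test a one-sided Cochran-Mantel-Haenszel test stratified by surgical sub-specialisation, at the same 5% level.
- Report the Mantel-Haenszel risk difference with its confidence interval as the estimate.
- Prespecify that gynaecology is merged with a named other stratum if either arm has no patient in it. At the pilot share it would supply about 82×1/37 = 2.2 patients, and a stratum with an empty arm contributes nothing to the stratified test.
- Keep the plain two-proportion z-test as a sensitivity analysis.

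The cost is a few sentences in 10.1, with no extra patients and no new data, because the specialty is already entered at randomisation. If the strata do not differ, the price is about half a power point (79.9% against 79.3% with random stratum sizes), or up to about 0.8 point with the fixed 27/13/1 split and the unrounded critical value.

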### 10.2 Secondary study parameter(s)

- Time from having the surgical field prepared for lymph node localization to actual removal of the lymph node: two-sample t-test,
- Overall surgery time: two-sample t-test
- The number of individual retrieved LN s in both arm, two-sample t-test
- Blood loss: two-sample t-test on all subjects
- Operator satisfaction: will be evaluated using standard questionnaires in the patients which are operated with navigation only. The questionnaire results in a score between 0 and 100. Technology which has a score 70 or higher is deemed beneficial [15].
- The QLQ and EQ-5D questionnaires are presented as a score from 0-100. Per arm these numbers will be handled as a continuous variable. We will also compare the change in the scores between T0 and T3 months, T0 and T6, and between T0 and T12 months at a patient level per arm. A two-sample t-test will be used for statistical evaluation

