## 5. TREATMENT OF SUBJECTS

All included patients are already scheduled for surgery. Participation will not influence the waiting time. If patients decide to participate, additional burden is dependent on randomization. All patients will be asked to take quality of life and side effects questionnaires before surgery and at 3 and 12 months after surgery. The questionnaires take approximately 20 minutes per time point.

Patients who are randomized to the conventional arm will be operated according to current clinical practice. These patients will undergo one additional CT scan with contrast (10 minutes) in the two weeks before surgery on which the target lymph nodes will be indicated. In the control arm, no 3D anatomical models will be generated.

Patients in the experimental arm will be operated with assistance of the in-house developed navigation system. One extra contrast enhanced CT scan before surgery will be acquired in the two weeks before surgery (10 minutes). During surgery, three Patient Trackers are attached to the skin of the patient using medical tape, not obstructing the surgical field. An additional intra-operative CT scan is acquired ( $\pm 10$  minutes) for calibration, which will be an addition to the total time of

anaesthesia. The surgeon will have a sterile tracked navigation pointer which can be used to correlate the actual anatomy of the patient with a 3D model derived from pre-operative imaging (Fig. 2). With this setup, the surgeon is provided with a view beyond surgical plane. After opening the abdomen, some anatomical landmarks will be used to verify the navigation accuracy, which will take a maximum of 5 minutes. Subsequently, the navigation system can be used to localize the targeted lymph nodes.

We will try to plan the additional pre-operative CT scan on a day at which the patient is already scheduled to visit our hospital to limit the travel time. Logistical challenges might result in an additional hospital visit.

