#### **8.1.2 Secondary study parameters/endpoints**

Time to localization: to assess the time to localization, the surgeon will be asked to indicate when he/she is ready to start localizing a targeted LN. The start point is after opening the abdomen, clearance of adhesions, installation of an abdominal wall retraction device. Time will be recorded until the LN is localized, and also until the LN is removed.

Other parameters which will be recorded are: success rate of retrieved individual LNs, overall surgery time from start of surgery until the abdomen is closed again; blood loss; technical failures of the navigation system; and operator satisfaction using standard questionnaires. For health technology assessment, EQ-5D-5L, QLQ-C30, and QLQ-CR29 or QLQ-PR25 will be used before surgery, and at 3 and 12 months

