### In the OR:

- Experimental arm: in the OR the patient will be placed on a dedicated navigation table with a carbon fibre imaging part and the EM field generator will be integrated in the mattress. With the table it is possible to have straight, fixed leg supports, or adjustable

leg holders for French position in bowel surgery. Preparation of the OR table is responsibility of the **researcher**.

- Experimental arm: before surgery, two electromagnetic Patient Trackers will be placed on the back of the patient, left and right from the spinal column. A third Patient Tracker is positioned at the anterior side at the level of the pubic bone. (Responsibility of the **researcher**)
- Experimental arm: after the patient is anesthetised and positioned for surgery a 3D XperCT scan (no contrast fluid used) is acquired. (Responsibility of the **researcher**, **maximum 10 minutes**)
- Experimental arm: the 3D XperCT scan is registered to the planning CT based on bony anatomy. After registration, the locations of the Patient Trackers are determined. Subsequently, the navigation setup is standby for use. (Responsibility of the **researcher**)
- The trial arm of the patient is determined and surgery can start. (Responsibility of the **researcher**)
- Experimental arm: the accuracy of the navigation system is first checked by pointing at bony landmarks, such as the pubic bone, iliac spine, promontory, and/or the large vessels (e.g. the position of the aortic bifurcation or common iliac bifurcations). If needed, the navigation settings can be adapted in the software to improve accuracy. This process will take at most **5 minutes**. (Responsibility of the **surgeon and researcher**)
- All patients: During surgery, the following time points will be noted: start of surgery, surgical field ready for LN localization, LN localized, LN removed, end of surgery. (Responsibility of the **researcher**)
- Experimental arm: At the end of the surgery, the Patient Trackers are removed. (Responsibility of the **researcher**)
- Experimental arm: The surgeon/urologist is asked to fill out the satisfaction questionnaire. (Responsibility of the **researcher**)

After surgery:

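### The t-test on time to node removal has no value for nodes never removed, which are expected more often under control, and neither time endpoint counts the navigation set-up done before surgery starts

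*Protocol*

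**What the plan says.** **Test.** Section 10.2 lists "Time from having the surgical field prepared for lymph node localization to actual removal of the lymph node: two-sample t-test" and "Overall surgery time: two-sample t-test". It gives no rule for a node without a removal time and does not say whether the unit is the node or the patient.

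**Clock for removal.** Section 8.1.2: "The start point is after opening the abdomen, clearance of adhesions, installation of an abdominal wall retraction device". For the end of the interval: "Time will be recorded until the LN is localized, and also until the LN is removed". Section 8.3 lists five time stamps: start of surgery, field ready, node localized, node removed, end of surgery.

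**Clock for the whole operation.** Section 8.1.2: "overall surgery time from start of surgery until the abdomen is closed again".

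**Nodes that are not removed.** Section 4.4 reports that 4 of 71 pilot nodes, in four of 25 patients, were not localized. It adds at least six patients in whom surgeons thought certain nodes would have been missed without navigation. Sections 8.1.1 and 10.1 foresee nodes judged inoperable during surgery and keep them in the primary analysis.

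**Navigation set-up.** Section 8.3 places tracker placement, CT and registration in the experimental arm ahead of the step that lets surgery begin: "after the patient is anesthetised and positioned for surgery a 3D XperCT scan (no contrast fluid used) is acquired", with a duration of "maximum 10 minutes". Section 5 gives about 10 minutes and says this scan lengthens anaesthesia. Section 5 also says that, once the abdomen is open, "some anatomical landmarks will be used to verify the navigation accuracy, which will take a maximum of 5 minutes".

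**The concern.** Section 5.1 makes faster localization part of the trial's hypothesis, and sections 6.4 and 11.4 present speed as a benefit. Two separate mechanisms affect how the time results can be read.

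First, time to removal exists only for nodes that were removed. If navigation turns failures into slow successes, those successes enter the navigation mean, while the matching failures drop out of the control mean. Randomization does not protect a comparison that is restricted, after treatment, to successes.

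Second, overall surgery time leaves out work that occurs in one arm only and that the protocol itself says prolongs anaesthesia. A difference in this endpoint could be taken for total time saved when it is not.

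The first mechanism acts on time to removal and would probably work against navigation. The second acts on any reading of the results as total time and works in its favour.

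**Working it through.** **1. The plan's own figure.** The only calculation in the protocol is the primary sample size. With unpooled variance and one-sided alpha 0.05:

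n = (0.40×0.60 + 0.16×0.84) × (1.645 + 0.842)² / 0.24² = 40.2, rounded up to 41 per arm.

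This reproduces the stated 41. The protocol gives no mean, SD or sample size for any time endpoint.

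**2. Share of nodes without a time.**
- Navigation: 4/71 = 5.6% (section 4.4).
- Control: (4 + 6)/71 = 14.1%, *assuming* one extra missed node in each of the at least six patients.
- Nodes per patient in the pilot: 71/25 = 2.84.

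Nodes left as inoperable would add to both shares. The protocol gives no rate for them.

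**3. Illustration with no true difference.** Assumptions: the mean is 30 minutes in both arms, the slowest share q of nodes is never removed, and those nodes are dropped. The mean of the observed times is:
- exponential: 30 × (1 − q + q ln q)/(1 − q)
- log-normal with log-SD s: 30 × Φ(z − s)/(1 − q), where z is the 1 − q normal quantile (1.077 for control, 1.586 for navigation).

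| Distribution | Control, q = 14.1% | Navigation, q = 5.6% | Navigation looks slower by |
|---|---|---|---|
| Exponential | 20.4 | 24.8 | 4.5 min |
| Log-normal, s = 0.5 | 25.1 | 27.4 | 2.3 min |
| Log-normal, s = 1 | 18.5 | 22.9 | 4.4 min |

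In simulation with 41 independent times per arm before the drop, the two-sided 5% t-test declared navigation slower in 14% (s = 0.5) and 18% (s = 1) of trials. The nominal figure is 2.5%.

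**4. Illustration with a true gain.** Assumptions: log-normal times with log-SD 0.8, every search abandoned at 45 minutes, and medians set to give the same missing shares.
- Medians: 45 × exp(−0.8 × 1.077) = 19.0 minutes under control; 45 × exp(−0.8 × 1.586) = 12.6 under navigation.
- Mean with unremoved nodes counted at 45 minutes: 22.3 v 16.2, a gain of 6.1 minutes.
- Mean in removed nodes only: 18.6 v 14.5, a gain of 4.1 minutes.
- Lost: (6.1 − 4.1)/6.1, about one third.
- Simulated two-sided power with 41 independent nodes per arm: about 40% for the t-test on removed nodes, about 60% for a rank test with unremoved nodes placed last.

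**5. Set-up against the two clocks.**

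| Step (navigation arm only) | Overall surgery time | Field ready to removal |
|---|---|---|
| Tracker placement (duration not stated) | outside | outside |
| CT, about 10 minutes (section 5), at most 10 (section 8.3) | outside | outside |
| Registration (duration not stated) | outside | outside |
| Landmark check, at most 5 minutes | inside, because it follows opening | not stated |

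Sections 5 and 8.1.2 both place their event after opening, but they do not order the landmark check against adhesiolysis, retractor placement and the surgeon's declaration of readiness.

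**The case against.** The best case for the plan has four parts.

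*Unremoved nodes need not be long searches.* Section 6.3 explains the four pilot misses: three nodes had shrunk below 3 mm and one was probably not rigid enough. Section 8.1.1 ties inoperability to expected morbidity, not to elapsed time. This stands: the direction of the bias is a plausible premise that the documents do not establish. That the two groups compared are selected on success does not depend on it.

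*A statistical analysis plan could settle absent times.* In part. But the protocol names the test and fixes the time stamps, and a later plan cannot analyse an abandonment time that was not recorded.

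*A clock starting at field ready suits a hypothesis about localization.* Agreed. That start point is a legitimate definition, and section 5 openly reports the added anaesthesia time. The gap is that no endpoint measures that time.

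*The endpoint is secondary.* Agreed.

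A reader might also infer more than the documents support:
- *That 40% against 16% is the share of missing times.* It is procedure-level failure read from follow-up imaging. A node recorded as removed but still visible later has a time, and a failed procedure may have other targets with times.
- *That both clocks omit all set-up.* The landmark check lies inside overall surgery time.
- *That the check lies outside the removal clock.* Its place is not stated.
- *That at least 10 minutes of scanning are lost.* Section 8.3 gives 10 as a maximum and section 5 as approximate.

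**Conclusion.** The point holds in two limited parts.

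The t-test on time to removal can use only removed nodes. The protocol's own pilot reasoning implies more unfound nodes under control (14.1% against 5.6%, under the one-node-per-patient assumption), so the comparison is conditioned on success unequally by arm. If the missing times are mostly long ones, navigation's benefit is understated. The minutes shown above rest on assumed distributions, an assumed cut-off and independent nodes, so they illustrate the problem and do not estimate the bias.

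Tracker placement, CT and registration fall outside both time endpoints. About 10 minutes of CT, plus an unstated amount, is missing from any reading of overall surgery time as total time saved. As a measure of start of surgery to closure, that endpoint remains valid and has a value for every completed operation.

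The two effects oppose each other and act on different readings. The documents do not fix a net sign. The primary analysis is unaffected.

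**What to change.** - **Record** the time at which a search is abandoned or a node is declared inoperable, alongside the stamps in section 8.3.
- **Analyse** removal as time-to-event with abandonment as an unsuccessful end: compare the cumulative incidence of removal, or rank unremoved nodes worst. Do not treat abandonment as ordinary censoring. Allow for several nodes per patient (patient as the cluster) and stratify by surgical specialty, as the randomization does.
- **Add** total anaesthesia or operating-room time in both arms, from an event that both arms share and that precedes tracker placement and the CT, up to closure. Do not report overall surgery time as total time saved.
- **State** on which side of the field-ready point the landmark check falls. Keep the same start event for the localization clock in both arms; starting it earlier in the navigation arm alone would create a new imbalance.

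Cost: one or two extra time stamps, taken by the researcher who already records times in both arms, and revised wording in sections 8.1.2, 8.3 and 10.2. Counting set-up will make the total-time result somewhat less favourable to navigation.
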